### Blinding

Blinding is not possible as the intervention is a multifactorial approach. That’s why the control group is selected after the intervention is made but for the same period of time.

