## Methods/design

### Study design

Experimental design. Type of study: open randomized clinical trial. Follow-up period: one year.

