### Participants

Setting: Primary Health Care. Valencian Community (Spain).

15 Health centers: Alicante-Cabo-Huertas, Alicante-Campello, Alicante-Plà Hospital, Castellón-Dolores-Cano-Royo-Villareal, Castellón-La-Bobila-Villareal, Castellón-Cariñena-Villareal, Castellón-Nules, Castellón-Vall d’Uxo I and II; Valencia-S Pau, Valencia-R-Argentina, Valencia-Benimaclet and Valencia-Serreria-II.

Inclusion criteria: patients with a diagnosis of IHD of any site (ICD-10 codes from 410 to 414 inclusive); age from 30 to 80 years; signed written informed consent. Exclusion criteria: lack of consent; immobilized patients; patients with serious health problems or with a low life expectancy.

Data are collected from electronic health record system.

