### Randomization, allocation and implementation

Valencia is a Mediterranean Spanish Region with 5 million inhabitants. In 2007, 800 primary care physicians and nurses started the ESCARVAL primary prevention cohort study [20]. 72 Health centers (HC) participated including 50000 patients.

For the intervention group in the PROPRESE study 15 HC are selected from those participating in ESCARVAL. Once the center agreed to participate patients are randomly selected from the total amount of patients with IHD registered in the electronic health records.

For the control group a random sample of patients with IHD is selected from all 72 HC electronic records.

Patients are enrolled by their primary care physicians who will offer to participate to the randomly selected patient.

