	**Control group:**		
	A random sample of patients (350) with IHD selected from 72 HC electronic records (from ESCARVAL-risk study)		
**Intervention follow-up: 1 year**	Baseline data		
	Personalized follow-up record		
	Starting formative intervention strategy for professionals and patients:		
	**Intervention**	**Patients**	**Professionals**
	**First visit**	Evaluate monitoring of CVRF	Advice online by cardiologist
		Accord control objectives	Monthly updates
		Adherence control	Protocols, guides and bibliography reviews
		Therapeutic education	In-class training course
	**Second visit**	Evaluate monitoring of CVRF	Advice online by cardiologist
		Accord control objectives	Monthly updates
		Adherence control	Protocols, guides and bibliography reviews
		Therapeutic education	In-class training course
	**Third visit**	Evaluate monitoring of CVRF	Advice online by cardiologist
		Accord control objectives	Monthly updates
		Adherence control	Protocols, guides and bibliography reviews
		Therapeutic education	In-class training course
		Number of hospital admissions	
**Outcomes**	Statistical analysis. Loses to follow-up.		
	Presentation of results at participating HC.		
	Final report		

*HC*, Health Center.

**Table 5 T5:** Functions of the professionals participating in the study

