#### Informed consent

All patients must read the “Patient Information Form” and sign a document giving their consent.

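### Controls are selected after the intervention year while signed consent is required of everyone, so as written the two arms have different time zeros and the hospitalization comparison can be biased

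*Protocol article*

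**What the plan says.** All references are to the protocol article.

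- **Timing of control selection.** Blinding explains that the intervention cannot be masked and gives this as the reason why "the control group is selected after the intervention is made but for the same period of time".
- **Length of the period.** Study design gives "Follow-up period: one year"; Table 4 has "Intervention follow-up: 1 year".
- **Intervention arm.** Randomization, allocation and implementation: "Once the center agreed to participate patients are randomly selected from the total amount of patients with IHD registered in the electronic health records".
- **Control arm.** Same section: "For the control group a random sample of patients with IHD is selected from all 72 HC electronic records".
- **Enrolment.** Same section, with no arm named: "Patients are enrolled by their primary care physicians who will offer to participate to the randomly selected patient".
- **Eligibility.** Participants makes signed consent an inclusion criterion, limits age to 30 to 80 years, and lists "Exclusion criteria: lack of consent; immobilized patients; patients with serious health problems or with a low life expectancy".
- **Consent.** Informed consent says that all patients must read the information form and "sign a document giving their consent". It makes no exception for controls.
- **Primary outcome.** Outcome measures names the number of hospitalizations, by cause.
- **Table 4.** Both groups appear in the enrolment block, ahead of the follow-up year. Physician enrolment and the eligibility criteria are mentioned only for the intervention group. The control entry describes only a random sample of 350 from the records of the 72 centers.

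**The concern.** In a comparison over a fixed year, both arms should be eligible, and start to be counted, at the same point. Here one arm is entered before the year and the other after it. If entry depends on being alive, reachable and willing to sign, controls have to pass that test a year later than intervention patients.

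Patients who die or deteriorate during a year with ischemic heart disease are likely to be those admitted most often. Removing them from one arm only would distort the primary outcome. A larger sample does not remove such a distortion. The multivariate analysis named under Statistical analysis cannot recover patients who never entered the control sample.

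Late selection is offered as the response to the lack of blinding. It may keep control physicians unaware of the study during the year. It does not blind patients, treating staff or assessors in the intervention arm, and it creates the difference in time zero.

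**Working it through.** **Setting the sections side by side**

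1. Blinding places control selection after the intervention, for the same period. With a one-year intervention, I read this as selection once the year is complete, with control data taken from that past year.
2. Randomization, allocation and implementation, with Table 4, places selection and enrolment of intervention patients before their year begins.
3. Participants and Informed consent require a signature from every patient. A patient selected after the year can sign only if alive and reachable then. Steps 1 and 3 together make survival through the outcome year a condition of entry for controls. Step 2 shows that intervention patients face no such condition.
4. Immobility, serious health problems and low life expectancy are exclusions related to prognosis. No section says on which date they are judged for controls. They may be judged at year-end, which would add to the asymmetry, but this is an inference.
5. Table 4 points another way: controls are listed ahead of follow-up, and neither enrolment nor criteria are mentioned for them. If controls are record-only, survival is not imposed, but Participants and Informed consent are then contradicted.

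The text therefore supports two control groups that differ in who is in them.

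**Size under assumed inputs**

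The article gives no mortality or admission rate and no expected effect on hospitalizations, so there is no figure of its own to reproduce on this point. Every input below is an assumption.

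Let m be the share of patients who die during the year, hs the admissions per survivor and hd the admissions per patient who dies. With no true effect, all intervention patients counted and controls limited to survivors:

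- intervention rate = (1 − m) × hs + m × hd
- control rate = hs
- ratio = intervention rate / control rate

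| m | hs | hd | Intervention rate | Control rate | Ratio |
|---|---|---|---|---|---|
| 0.02 | 0.2 | 1.0 | 0.98 × 0.2 + 0.02 × 1.0 = 0.216 | 0.2 | 1.08 |
| 0.04 | 0.2 | 1.0 | 0.96 × 0.2 + 0.04 × 1.0 = 0.232 | 0.2 | 1.16 |
| 0.06 | 0.1 | 1.0 | 0.94 × 0.1 + 0.06 × 1.0 = 0.154 | 0.1 | 1.54 |
| 0.08 | 0.1 | 1.5 | 0.92 × 0.1 + 0.08 × 1.5 = 0.212 | 0.1 | 2.12 |

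The unbiased ratio is 1.00. Over m of 2–8%, hs of 0.1–0.2 and hd of 1.0–1.5, the first and last rows are the extremes. On this mechanism the intervention looks worse than it is.

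Two variations show that the result depends on which reading is correct:

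- If intervention patients who die are also dropped from the analysis, both rates equal hs and the ratio returns to 1.00.
- If controls are record-only and unscreened, let m be the share with a prognosis-related exclusion, with hd their admissions. The control rate becomes (1 − m) × hs + m × hd against hs in the screened intervention arm. The same inputs then give 1/1.08 = 0.93 down to 1/2.12 = 0.47, which favors the intervention.

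**The case against.** The strongest reply is that Blinding says when controls are selected, not when their eligibility is judged. Because data come from the electronic record, a frame dated to the start of the year is compatible with the wording, and a condensed article may leave the query's index date to the full protocol. This stands for the age, immobility, serious-illness and life-expectancy criteria. It does not stand for consent: the article requires it of everyone, and it cannot be given retrospectively by someone who has died.

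Several stronger readings are tempting and are not supported:

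- *All exclusions are applied to controls at year-end.* No section says so; the date is simply not fixed.
- *The control admission rate is certainly understated.* Table 4 may describe unscreened record-only controls, which would raise it. Selective late consent, or patients first diagnosed during the year, could also shift it.
- *Intervention patients who die or deteriorate are kept while their control counterparts are not.* No section says that they are kept. Sample size allows 20% for losses and Table 4 lists losses to follow-up.
- *Control risk-factor levels come from a healthier survivor set.* Year-end measurements exist only for living patients in both arms, so deaths alone do not create this difference.
- *Controls are chosen with knowledge of their outcome.* The sample is stated to be random. Knowledge of admissions could act only through the offer and consent step.

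**Conclusion.** The point holds as a conflict within the article that bears on the primary comparison. As written, late control selection combined with universal signed consent gives the arms different time zeros and makes survival of the outcome year a condition of control entry. This is a stated design rule, not a detail left to another document. It rests on reading the Blinding sentence as selection after the full year, which its reference to the same period supports.

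The direction is not settled. Consenting survivors as controls would probably understate control admissions and mask a benefit; unscreened record-only controls could overstate them and flatter the intervention. The size cannot be obtained from the documents. The ratios of 1.08 to 2.12, and their reciprocals, are hypothetical and show only that the bias need not be small. Late selection does not resolve the lack of blinding on either reading. The case for a common index date does not depend on the sign of the bias, and it should be settled before controls are drawn.

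**What to change.** 1. Late extraction can stay, but define the control sampling frame as of the intervention start date: patients registered with ischemic heart disease and within the age range on that date.
2. Apply every eligibility criterion to controls as of that date, using only data recorded up to it.
3. Keep in the analysis, in both arms, patients who later die or become ineligible. Count admissions and person-time from the index date.
4. Reconcile Participants, Randomization, allocation and implementation, Blinding, Table 4 and Informed consent on whether controls are approached, screened and asked to sign, so that consent does not bring survival back in as an entry condition.
5. In Blinding, stop presenting late selection as the answer to the open design.

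**Cost.** The data work is small: a redated query on electronic records that the trial already uses. The consent change is the larger part. Deceased controls cannot be retained while signed consent is an eligibility criterion for everyone, so that criterion must be amended for record-only controls and may need ethics committee approval.

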### Statistical analysis

The results are expressed as frequencies and percentages for qualitative variables and as mean and standard deviation for the quantitative variables. For the statistical analysis, the study of categorical variables is carried out by the ×^2^ test and the comparison of the continuous variables between groups of patients by the Student t test and ANOVA. A multivariate analysis will be carried out to evaluate the effect of the intervention. The SPSS PC 15.0 program will be used.

The reference search was performed in the Medline database through PubMed. The MeSH terms used were: “Myocardial Ischaemia/prevention and control” [Mesh]” OR “Myocardial Ischaemia/epidemiology” [MeSH], OR “Coronary Artery Disease”[MeSH Terms] AND “Secondary prevention”. A second search included: “Patient Education” as Topic/methods OR “Patient Participation” OR “Self-Help Groups” OR “Program Evaluation” AND “Myocardial Ischaemia”.

In the Cochrane database we used the MeSH terms: Patient Education, Lifestyle.

The search was limited to publications in the last 5 years, only items with abstracts, studies in humans, and a publication type of Meta-Analysis and Systematic Review. In the Cochrane database we also used the search limit of the last 5 years.

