### Outcome measures

Primary outcome measure: number of hospitalizations/cause. It is measured at the beginning and end of the study.

Secondary outcomes:

a) Level of control of CVRF: Blood pressure, LDL cholesterol, body mass index, basal blood glucose, HbA1c, therapeutic compliance (pill count), smoking. They are measured at each visit.

b) Healthy life habits: Exercise, mediterranean diet. They are measured at each visit.

c) Management: Number of annual primary care visits. It is measured at the end of the study.

To enhance the quality of measurements a training program is performed and there was one assessor for every three health centers.

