### Sample size

The calculation of the sample size is carried out to compare means, with an alpha risk of 0.05 (95% confidence level) and a beta risk of 0.20 (80% power). For an estimated difference in SBP of 5 mmHg and a standard deviation of SBP of 2.5 mmHg, the number of persons necessary is 251 patients per group. Increased by 20% for possible losses, giving a total of 301 patients in each group.

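### The hospitalization count is the primary outcome, but none of the named tests uses time at risk or the baseline count, so unequal follow-up between arms would bias the comparison

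*Protocol article*

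**What the plan says.** Protocol article, Outcome measures: "Primary outcome measure: number of hospitalizations/cause. It is measured at the beginning and end of the study". This is an event count with a value at each end of the study. A second count is listed among the secondary outcomes: "Number of annual primary care visits. It is measured at the end of the study".

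Protocol article, Study design: "Type of study: open randomized clinical trial. Follow-up period: one year".

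Protocol article, Statistical analysis, names three tests and one further analysis:

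- Chi-square, in the clause that begins "the study of categorical variables is carried out by the".
- Student t and ANOVA, in the next clause: "the comparison of the continuous variables between groups of patients by the Student t test and ANOVA".
- One further analysis, described in a single sentence: "A multivariate analysis will be carried out to evaluate the effect of the intervention".

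That sentence gives no outcome, model, covariates or person-time term.

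Protocol article, Sample size, allows for incomplete follow-up: "Increased by 20% for possible losses". Table 4 lists losses to follow-up beside the statistical analysis, without saying how they are handled.

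Two features of the design bear on follow-up. Under Randomization, allocation and implementation, intervention patients come from 15 health centers and controls from all 72 in the parent cohort. Under Blinding, controls are chosen once the intervention has been delivered, though for the same calendar period.

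**The concern.** A count of admissions depends on how long each patient was observed. A t test or ANOVA on raw counts has no place for that time, and neither has a chi-square on any admission versus none. If the arms are observed for different lengths of time, the arm observed for less shows fewer admissions even when the intervention does nothing.

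The design makes unequal observation plausible. Intervention patients are enrolled by their physicians and followed forward for a year, so they can be lost. Controls are picked afterwards. The Participants and Informed consent sections ask for signed consent from all patients. If that includes controls, those selected at the end must be alive and reachable, and few would count as lost. This is an inference from the design, not a stated fact. The resulting bias would favour the intervention.

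The admission count at the start is also left idle by a two-group test on the final counts. It has a use beyond precision, because the arms come from different sets of centers and may differ in admissions before the study.

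**Working it through.** **1. The plan's own figure.** No figure is given for hospitalizations. The only calculation is for systolic blood pressure: difference 5 mmHg, SD 2.5 mmHg, alpha 0.05, power 80%, stated result 251 per group. The standard formula is n = 2 × (1.96 + 0.8416)² × (SD/difference)².

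- As stated: 15.70 × (2.5/5)² = 3.9, so 4 per group. The 251 is not reproduced.
- With SD 20: 15.70 × (20/5)² = 251.2, so 251 implies an SD of about 20.

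That is a separate matter. It enters here only as the source of the arm size: 251 × 1.2 = 301.2, stated as 301.

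**2. Inputs for this point.** From the protocol article: 301 per arm, one year of follow-up, 20% losses. Assumed, because the article gives none of them: 0.1-0.6 admissions per patient-year, overdispersion, and losses at uniform times in the year. Variance is taken as m + k·m², with m the mean count and k = 1 or 2 where losses are unequal. Tests are two-sided at 5%.

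**3. Does a skewed count break the t test?** With complete follow-up and no effect, simulation (4,000 runs per scenario, k = 0 to 2, rates 0.1 to 1.0, 37-91% of patients with no admission) gave rejection of 4.5-5.6%. It does not.

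**4. Do equal losses bias it?** With 20% lost in both arms and no effect, the ratio of mean counts was 0.99-1.00 and t-test rejection 4.4-5.4%. With a true rate ratio of 0.70, the estimated ratio stayed at 0.70. The absolute difference shrank by about 10% (from -0.061 to -0.054 at 0.2 per year; from -0.151 to -0.134 at 0.5 per year). Power was 34.2% for the t test and 34.7% for the rate analysis at 0.2 per year, and 60.1% and 61.4% at 0.5. There is no null bias, and the offset adds little power.

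**5. Do unequal losses bias it?** If a share d leaves at uniform times, mean observed time is (1 - d) × 1 + d × 0.5 = 1 - d/2.

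- 20% vs 0%: 0.90/1.00 = 0.90.
- 20% vs 5%: 0.90/0.975 = 0.92.

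These are the ratios of mean raw counts with no effect of treatment.

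A hand check of the rejection rate at m = 0.3, k = 1, 20% vs 0%:

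- Variance = 0.3 + 0.09 = 0.39.
- SE of the difference = √(2 × 0.39/301) = 0.0509.
- Spurious difference = 0.10 × 0.3 = 0.03, or 0.589 SE.
- Rejection = Φ(-1.96 + 0.589) + Φ(-1.96 - 0.589) = 0.085 + 0.005 = 9.1%.

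Simulated null rejection, 301 per arm:

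| Loss | Admissions/year | t test on counts | Rate analysis with person-time |
|---|---|---|---|
| 20% vs 0% | 0.1 | 6.4% | 4.7-5.0% |
| 20% vs 0% | 0.2 | 7.6-7.8% | 5.0-5.5% |
| 20% vs 0% | 0.3 | 8.8-9.0% | 5.0-5.2% |
| 20% vs 0% | 0.5 | 8.9-11.3% | 4.6-5.1% |
| 20% vs 5% | 0.3 (k = 1) | 8.0% | 5.1% |

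The person-time rate ratio in these runs was 0.99-1.01. A separate simulation (1,500 runs per scenario) at 0.6 per year with k = 2 gave 10.6% for the t test and 5.6% for the offset model.

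**The case against.** The strongest reply is that the multivariate analysis is the one analysis the article links to the intervention effect. It could be a count model with an offset and the baseline count, and an article may leave its form to an analysis plan that is not shown. It is fair that the article does not rule such a model out. But it does choose tests, those tests do not fit the outcome it calls primary, and the multivariate sentence commits to nothing that would make up for this.

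A second reply is that follow-up may be nearly complete or equal. Data come from the electronic record, the period is a fixed year, and the sample size plans the same 20% in each group. A patient who misses visits need not lose admission data. Adding patients for losses may also mean that lost patients are left out, in which case everyone analysed has a full year. These points stand, and they make the bias conditional. The 20% versus 0% split is the extreme case within the planned allowance.

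Three stronger readings are tempting. A reader might infer that most patients have no admissions and that this alone invalidates the t test. The article gives no admission rate or share of zeros, and step 3 shows the test keeps its size across a wide range. A reader might infer that any incomplete follow-up biases the comparison. Step 4 shows that equal losses do not do so under the null. A reader might also infer that the trial will report a false reduction in admissions. The documents do not say how losses are handled or that they will differ between arms.

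**Conclusion.** The point holds in a conditional form. The article ties no analysis to its primary outcome, and the tests it names use neither time at risk nor the count taken at the start. If follow-up differs between arms, the raw-count comparison is biased in favour of the arm with more loss. At 20% versus 0% loss the bias in the ratio is about 10%, with t-test rejection of about 6-11% instead of 5% for 0.1-0.6 admissions per year. At 20% versus 5% and 0.3 per year it is about 8%, with 8.0% rejection.

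The admission rates, the dispersion and the uniform timing of losses are assumptions. Under those assumptions the ratio depends only on observed time; the rejection rate also depends on the admission rate, dispersion and arm size. The case for change rests on protection against this bias and on use of a baseline value already collected, not on power. It is a cheap improvement that should be made.

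**What to change.** State that the multivariate analysis of hospitalizations is a negative binomial regression, or a Poisson regression with robust standard errors, with:

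- arm as the effect of interest;
- log of observed person-time as offset;
- the beginning-of-study admission count as covariate, over a look-back period that the plan defines, since none is given now;
- the rate ratio with its 95% CI as the reported result.

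State how losses enter the analysis and how the end of observation is defined in each arm. Use the same offset for annual primary care visits if follow-up is incomplete. The t test can stay for the continuous risk-factor outcomes.

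The cost is a few sentences, slightly more analysis, and extraction of each patient's end-of-observation date. The article does not say that this date is held, so its availability should be checked. If follow-up proves complete, the offset changes nothing. It does not cure the selection of controls who survived the period, which needs separate attention in how controls are defined.

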a) Formative. Four face-to-face workshops (every 3 months); monthly clinical session on cardiovascular disease; online tutorials with the cardiology service to solve any doubts. Face-to-face tutorials with a team, reference doctor/nurse, in each health center.

a) Strategies to avoid clinical inertia: carry out therapeutic changes if there is poor control before 3 months.

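### The intervention arm is made up of patients clustered in 15 selected health centers, but the sample size and the named tests treat all patients as independent

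*Protocol article*

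**What the plan says.** The Randomization, allocation and implementation section builds the intervention arm from centers: "For the intervention group in the PROPRESE study 15 HC are selected from those participating in ESCARVAL". Patients are sampled from a center's records once that center has agreed. Controls are sampled from the records of all 72 ESCARVAL centers. Table 4 gives 350 patients per arm; the Sample size section gives 301.

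The intervention is mixed. Personalized objectives and the follow-up record are set for each patient. The workshops, monthly clinical sessions, doctor-nurse teamwork and tutorials act on staff: "Face-to-face tutorials with a team, reference doctor/nurse, in each health center".

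The Sample size section states: "The calculation of the sample size is carried out to compare means, with an alpha risk of 0.05", at 80% power. The inputs are: "For an estimated difference in SBP of 5 mmHg and a standard deviation of SBP of 2.5 mmHg". The result is that "the number of persons necessary is 251 patients per group", raised to 301 for losses. No ICC, design effect or number of centers enters the calculation.

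The Statistical analysis section names chi-square for categorical variables and, for continuous ones, "comparison of the continuous variables between groups of patients by the Student t test and ANOVA". It adds a multivariate analysis of the intervention effect, without naming its model or any center term.

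**The concern.** Patients of one center share doctors, nurses, recording habits and, in the intervention arm, the same trained team. Their outcomes are therefore likely to be correlated. Student's t, ANOVA and chi-square assume that they are not.

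The correlation matters most in the intervention arm, where every patient sits in one of only 15 centers, at about 17, 20 or 23 per center for 251, 301 or 350 patients. Controls are spread thinly, at about 3.5 to 5 per center.

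The standard error of a between-arm difference is then understated. Confidence intervals are too narrow, a nominal 5% test rejects too often, and the stated power is too high for a test that does hold its 5% level. The tests are named for categorical and continuous variables in general, so no between-group comparison is exempt.

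**Working it through.** **Inputs from the protocol.** Alpha 0.05; power 80%; SBP difference 5 mmHg; printed SD 2.5 mmHg; 251 per group, 301 after the allowance for losses, 350 in Table 4; 15 intervention centers; 72 centers for control sampling.

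**Assumed.** ICC of 0.01, 0.02, 0.05 and 0.10, because the protocol gives none, and equal numbers per center.

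**Step 1: the plan's own figure.** n per group = 2 × [SD × (1.960 + 0.842) / difference]².
- With SD 2.5 and difference 5: 2 × (1.401)² = 3.9, so 4 per group. The printed inputs do not give 251.
- With SD 20 and difference 5: 2 × (11.21)² = 251.2, which matches 251 (standardized difference 5/20 = 0.25).
- 251 × 1.2 = 301.2, which matches 301.

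The variant that matches 251 has a design effect of 1, so no cluster allowance is hidden in it. The printed SD is a separate error and has to be settled first. SD 20 is used below only because it is what 251 implies.

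**Step 2: variance factor for the difference in means**, relative to independent patients.
- Controls from other centers (disjoint): V = (DE₁ + DE₀)/2, with DE = 1 + (m − 1) × ICC, m = n/15 in the intervention arm and n/72 in the control arm.
- Controls from all 72 centers including the 15 (shared): center effects partly cancel, and V = (1 − ICC) + ICC × (n/2) × (1/15 − 1/72).

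At n = 301, m is 20.1 and 4.2, and (301/2) × (1/15 − 1/72) = 7.94.

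**Step 3: type I error of the unadjusted test**, 2 × [1 − Φ(1.96/√V)], at 301 per arm.

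| ICC | DE₁ | DE₀ | V disjoint | Type I disjoint | V shared | Type I shared |
|---|---|---|---|---|---|---|
| 0.01 | 1.19 | 1.03 | 1.11 | 6.3% | 1.07 | 5.8% |
| 0.02 | 1.38 | 1.06 | 1.22 | 7.6% | 1.14 | 6.6% |
| 0.05 | 1.95 | 1.16 | 1.56 | 11.6% | 1.35 | 9.1% |
| 0.10 | 2.91 | 1.32 | 2.11 | 17.7% | 1.69 | 13.2% |

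A simulation of the unadjusted t test (20,000 runs per cell, controls drawn at random over centers) gave 6.0%, 7.9%, 11.9% and 18.2% disjoint, and 5.9%, 6.7%, 9.4% and 13.7% shared. The shared values run slightly above the formula because random draws make the control counts per center uneven.

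**Step 4: power of a correctly sized 5% test**, Φ(5 / [20 × √(2V/n)] − 1.96), disjoint centers. At 251 per arm, m is 16.7 and 3.5.

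| ICC | V at 251 | Power, 251 evaluable | Power, 301 evaluable |
|---|---|---|---|
| 0.01 | 1.09 | 76.5% | 82.9% |
| 0.02 | 1.18 | 73.1% | 79.2% |
| 0.05 | 1.46 | 64.1% | 69.1% |
| 0.10 | 1.91 | 52.6% | 56.0% |

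At 350 evaluable the same formula gives 87.5%, 83.7%, 72.9% and 58.6%. With the shared-center V and 251 evaluable it gives 77.8%, 75.7%, 69.7% and 61.1%. These values use the normal critical value; degrees of freedom tied to 15 centers would lower them somewhat.

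**Step 5: standard errors.** At 301 per arm with disjoint centers, √1.11 = 1.05 and √2.11 = 1.45, so they grow by about 5% to 45%.

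**The case against.** **The multivariate analysis could carry a center effect, and its model is the kind of detail an article leaves to an analysis plan.** This stands for the final effect estimate: one cannot say that it will ignore clustering. It does not rescue the rest. The t, ANOVA and chi-square comparisons are named, and the sample size is fixed on independent patients. Those are choices stated in the text, not details left out.

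**The inflation may be smaller than a simple two-arm design effect suggests.** This stands. A reader might take 12% and 18% at the two higher ICCs as the error rates of this plan. They require controls from centers other than the 15, whereas the protocol draws controls from all 72, and the 15 come from that set. With sharing, the rates are about 9% and 13-14%.

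**Power may still reach 80%.** This stands at low ICC. A reader might infer that the 80% is lost outright. At 251 evaluable it is, for every ICC assumed here. At 301 evaluable with disjoint centers it is kept at ICC 0.01 and just missed at 0.02, and at 350 it is kept at both.

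**The intervention is not purely center-level.** This is true: objectives and follow-up records are set patient by patient, and only sampled patients are enrolled. Describing it as delivered to whole centers goes too far. Clustering follows all the same, because entry to the intervention arm depends on the center and the staff components are shared within it.

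**Patients are sampled at random.** Random sampling within a center does not remove the correlation between patients of that center.

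**Conclusion.** The point holds and should be corrected. The intervention arm is nested in 15 centers, while the sizing and the named tests assume independent patients. The direction of the error follows from any positive ICC.

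Its size does not come from the protocol. It rests on an assumed ICC of 0.01 to 0.10, on whether controls come from the 15 centers, and on how many patients are evaluable. At 301 per arm, type I error is about 6% to 14% with shared centers and 6% to 18% with disjoint ones. The power figures also rest on SD 20, which is inferred from 251; with the printed SD of 2.5, power would be close to 100% even with clustering. They concern SBP, a secondary outcome. The effect on the primary outcome, hospitalizations, has the same direction but is not quantified here.

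Two conclusions that a reader might draw are not supported: that the higher error rates apply whatever the control sampling, and that 80% power is missed at every sample size in the protocol.

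**What to change.** - **Analysis.** Make the between-group comparisons with models that treat health center as the cluster: a linear mixed model for continuous outcomes; a negative binomial or logistic mixed model, or GEE with small-sample-corrected robust errors, for counts and binary outcomes. Take degrees of freedom that reflect the 15 intervention centers. Where a center contributes patients to both arms, give it one shared center effect.
- **Power.** Correct the SD first. Then restate power with arm-specific design effects over a stated ICC range, since one common design effect would misstate both arms. State whether controls may come from the 15 centers, because the result depends on it. This restates the power of the planned sample and does not call for more patients.
- **Cost.** A rewritten analysis paragraph, standard errors about 5% to 45% larger at 301 per arm (disjoint centers, ICC 0.01 to 0.10), and a less favourable stated power. No new data are needed, because patients are sampled through center records.
- **Limit.** The model corrects precision only. The 15 centers were selected and had to agree, and nothing says that they were randomized; a center-level model does not remove bias from that selection.
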